## Abstract

**Background:**

Ventricular fibrillation (VF) is a common arrhythmia that occurs after the release of aortic cross-clamp (ACC) in patients undergoing cardiopulmonary bypass (CPB) surgery. Repeated defibrillation and long duration of VF could increase myocardial injuries. In patients with left ventricular hypertrophy (LVH), VF is easier to occur and more difficult to be terminated. Amiodarone, known as class III antiarrhythmic agent, has the prominent properties of converting VF and restoring the sinus rhythm. Before ACC release, administration of amiodarone has been confirmed useful to reduce occurrence of VF. However, few studies are focused on the effect of amiodarone before ACC release on reducing VF in patients with LVH.

**Objective:**

This study aimed at determining the efficacy of prophylactic intravenous amiodarone administration on reperfusion VF after release of ACC in patients with LVH undergoing CPB surgery.

**Methods:**

This will be a prospective, randomized, double-blind, placebo-controlled trial. The trial will enroll 54 patients with LVH aged 18-75 years who will undergo CPB surgery. All eligible participants will be randomly allocated to either the amiodarone or placebo group by using the block randomization in a 1:1 ratio. The primary end point will be the incidence rate of VF 30 minutes after ACC release and be assessed using the Fisher exact test. All data will be analyzed in accordance with the intention-to-treat principle.

**Results:**

The study began in August 2022, and the data collection will take place for the next 2 academic years. As of this writing, 21 participants have already been recruited for the study.

**Conclusions:**

With this trial, we are hoping to demonstrate that prophylactic infusion of amiodarone before ACC release could reduce the occurrence of reperfusion VF in patients with LVH.

**Trial Registration:**

ClinicalTrials.gov ChiCTR2000035057; https://www.chictr.org.cn/showprojen.aspx?proj=57145

**International Registered Report Identifier (IRRID):**

DERR1-10.2196/40115

## Introduction

### Background

Ventricular fibrillation (VF) is commonly seen after aortic cross-clamp (ACC) release during cardiopulmonary bypass (CPB) surgery [1]. It has been reported that the incidence rate of VF after ACC release ranges from 45% to 100% [1-6]. Left ventricular hypertrophy (LVH) has been found to increase the incidence rate of VF after ACC release, which is more difficult to be terminated [7]. Internal electrical defibrillation is an effective method to eliminate VF but repeated shock and long duration of VF could aggravate myocardial injury and reduce the patient’s prognosis [8].

There are different factors leading to VF after ACC release including surgical trauma, insufficient myocardial protection, inadequate intracardiac deairing or left ventricular vent, abnormal electrolyte and acid-base metabolism, delayed rewarming before ACC release and myocardial reperfusion injury after ACC release, etc. Among these, myocardial reperfusion injury is the main reason resulting in VF after ACC release [9]. The ischemia of cardiomyocytes could cause the increase in extracellular potassium ions. When the blood supply is restored, the uneven recovery of extracellular potassium ions makes the cell membrane potentially unstable, which would easily lead to increased self-discipline or triggered arrhythmias [10]. At the same time, myocardial ischemia-reperfusion can increase intracellular calcium levels, resulting in delayed depolarization of cardiomyocytes and triggered electrical activity, which also induces ventricular arrhythmias. Furthermore, α-adrenergic receptors are activated in reperfusion cardiomyocytes over a short period of time, contributing to increased myocardial autonomic activity and intracellular calcium levels [11]. The ischemic cardiomyocytes gradually and slowly recover their activities after the blood resupply, during which they are prone to reentrant arrhythmias, and the effective refractory period of cardiomyocytes in ischemic regions decreases, which also provides conditions for the occurrence of reentrant arrhythmias [12]. Therefore, both reentrant and nonreentrant arrhythmias play a role in the occurrence of ischemia-reperfusion VF.

Long duration of VF has many side effects on cardiomyocytes after ACC release. A study showed that coronary artery blood supply was redistributed during VF, which resulted in subendocardial myocardial ischemia and cardiac dysfunction [13]. With the prolongation of VF duration, the resistance of subendocardial vessels increased gradually, which worsened the subendocardial ischemia of cardiomyocytes. Besides, myocardial edema also developed with the long duration of VF [14]. The ventricular wall tension and venous pressure would increase during VF and higher perfusion pressure would be required to achieve normal blood supply in CPB. Frequent and irregular myocardial contractions and increased pressure in the cardiac cavity could result in a higher oxygen consumption of myocardium. The abovementioned factors lead to the imbalance of oxygen supply and demand in myocardium, which seriously destroy the function of cardiomyocytes. Moreover, Khuri et al [15] discovered that metabolic acidosis was more severe in cardiomyocytes during VF and the postoperative mortality rate was higher in a group of patients. Creatine kinase–myocardial band (CK-MB) is a specific marker of myocardial injury. After ACC release, the postoperative CK-MB of patients with VF was significantly higher than that of patients without VF, and the degree of elevation was 75% related to the duration of VF [16].

Defibrillation could also damage the myocardium. Doherty et al [17] found that when the energy of defibrillation was more than 30 J, the damage of cardiomyocytes increased and the blood flow in cardiomyocytes decreased. Multiple defibrillations significantly increased myocardial damage compared with single defibrillation. The shorter time interval of each defibrillation also resulted in greater myocardial injuries. It was observed under electron microscope that the gaps between myocardial intercalated discs increased after defibrillation, thus affecting the myocardial contractile function. A clinical study showed that myocardial injury markers, cardiac troponin T, cardiac troponin I, and CK-MB were significantly elevated after cardiac shock, which further confirmed the myocardial injury owing to internal electrical defibrillation [18].

In patients with LVH, the volume of cardiomyocytes expands, but the corresponding coronary arteries do not increase, resulting in absence of subendocardial capillaries. The end-diastolic pressure and systolic cardiac function also increase, leading to increased myocardial oxygen consumption. These histological changes give rise to the imbalance of myocardial oxygen supply and demand, and ischemia of subendocardial myocardium, which reduces the tolerance of myocardium to ischemia-reperfusion [19]. Owing to the special structure of LVH, the perfusion fluid of CPB could not completely reach the subendocardial cardiomyocytes. Compared with the normal heart, the effect of myocardial protection during CPB is usually inadequate. The incidence of VF after ACC release increased significantly, and the energy and frequency of cardiac shocks in hypertrophic myocardium increased as well [20]. Thus, reducing the occurrence of VF has an important clinical significance.

Amiodarone is a class III antiarrhythmic agent with multiple electrophysiological effects, which has been used clinically in the management of both atrial and ventricular arrhythmias. Through hepatic metabolism, amiodarone is transformed to desethylamiodarone, which has the property of antiarrhythmic effects. Amiodarone is highly lipid soluble and is widely stored in fat, muscle, skin, liver, and lungs with a very long elimination half-life, averaging about 58 days [21]. The predominant antiarrhythmic effect of amiodarone is the inhibition of IKr and IKs channels leading to a prolongation of myocardial repolarization homogeneously. Amiodarone also slows heart rate and atrioventricular nodal conduction through inhibiting calcium channels and β-receptors. In addition, it also prolongs refractoriness and reduces intracardiac conduction velocity by blocking sodium channel [22,23]. It has been confirmed that intravenous amiodarone could protect myocardium from ischemia-reperfusion and prevent VF caused by reperfusion [24-26]. During ischemia-reperfusion, amiodarone can improve the metabolic efficiency of cardiomyocytes and reduce the repolarization dispersion of cell membrane, which is one of the main factors causing ventricular arrhythmias.

Previous studies have shown the effectiveness of amiodarone on reducing the incidence rate of VF after ACC release [2,3,27,28]. Samantaray et al [3] reported that during coronary artery bypass grafting surgery, 150 mg of amiodarone was given 3 minutes before aortic opening, which decreased the incidence of VF after ACC release compared with the placebo-controlled group. However, in the study of Ayoub and colleagues [2], the administration of amiodarone 2 minutes before aortic opening failed to reduce the incidence of VF after ACC release during coronary artery bypass grafting surgery, but lidocaine instead reduced the occurrence of VF. Mauerman et al [27] also found that neither 300 mg of amiodarone nor 1.5 mg/kg of lidocaine reduced the occurrence of VF. Furthermore, the study of Yilmaz et al [28] showed that both 300 mg of amiodarone and 1.5 mg/kg of lidocaine decreased VF after ACC release compared with the placebo-controlled group, but there was no significant difference in reducing VF between amiodarone and lidocaine groups. Although the results from the abovementioned clinical studies are controversial, they generally hint that amiodarone has a therapeutic effect on reperfusion VF after ACC release.

### Objective

The objective of this study is to explore the outcomes of prophylactic intravenous amiodarone administration on reperfusion VF after ACC release in patients with LVH undergoing CPB surgery.

This study also concentrates on the effect of amiodarone on hemodynamic state after weaning from CPB in patients with LVH, which few previous studies have examined.

## Methods

### Study Design and Setting

This study is a prospective, single-center, randomized, double-blinded, placebo-controlled clinical trial to investigate effect of perioperative intravenous amiodarone on reperfusion VF after release of ACC in patients with LVH undergoing CPB. The study will be conducted in the First Affiliated Hospital of Nanjing Medical University, Nanjing, China. A schematic of the trial protocol is presented in Figure 1.

**Figure 1 figure1:**
[figure not shown]
Trial flow chart.

### Study Population

Fifty-four patients who meet the eligibility criteria will be recruited and randomly divided into 2 groups, including amiodarone group (group A) and placebo-controlled group (group P), 27 cases in each group. Informed consent will be obtained from all participants (Textbox 1).

Inclusion and exclusion criteria of participants.
**Inclusion criteria**
Patients included in the trial are as follows:Subjects undergoing cardiopulmonary bypass surgeryAged between 18 and 75 yearsWith left ventricular hypertrophy diagnosed by transthoracic echocardiogram preoperativelyAmerican Society of Anesthesiologists class I-III
**Exclusion criteria**
Patients fulfilling one or more of the following criteria will not be included:Preoperative use of class I or III antiarrhythmic drugsCorrected QT interval of ≥480 milliseconds or QT of ≥500 millisecondsLeft ventricular ejection fraction <30%With thyroid dysfunctionWith electrolyte imbalancesWith hepatic or renal dysfunctionWith pulmonary interstitial fibrosisAllergic to amiodaroneUndergoing emergency surgeryUndergoing redo surgery

### Randomization and Blinding

Thirty minutes before ACC release, the enrolled participants who meet the eligibility criteria will be randomly allocated in a 1:1 ratio to 2 groups, namely, group A (treated with amiodarone) and group P (placebo control). Block randomization will be used with a block size of 4, which will be implemented with SPSS (version 22.0; IBM Corp) by an independent statistician, and the randomization numbers will be given to an external data manager with no involvement in the study procedures and concealed on password-protected computer.

When a patient meets the eligibility criteria, the external data manager will return the corresponding allocation to the nurse anesthetist. The drugs will be prepared by the nurse anesthetists according to the allocation information, packaged with the same looking and labeled with numbers, and injected by the anesthesiologists. Both anesthesiologists and patients will be blinded to the regimen. The anesthesiologist will be notified of the study group by the nurse anesthetists in case of emergency. However, the nurse anesthetists have no role in assessing the treatment actions, analyzing, or interpreting the data.

### Interventions

#### Treatment Regimen of Amiodarone

Thirty minutes before ACC release, the trial drugs will be administered through the central venous line. In group A, 150 mg of amiodarone will be diluted to 20 mL normal saline and pumped in 5 minutes. In group P, 20 mL normal saline will be pumped in 5 minutes (Table 1).

**Table 1 table1:** Schedule for enrolment and intervention per cluster.

Time point^a^		Enrollment	Allocation	Close-out			
		–*t*_1_	0	*t* _1_	*t* _2_	*t* _3_	*t* _4_
**Enrollment**							
	Eligibility screen	✓^b^					
	Informed consent	✓					
	Allocation		✓				
**Interventions**							
	Group A^c^			✓			
	Group P^d^			✓			
**Assessments**							
	Baseline demographic information	✓					
	Primary end point^e^				✓		
	Secondary end point^f^				✓	✓	✓

^a^Time point: *t*_1_: baseline; *t*_1_: intervention period, 30 minutes before aortic cross-clamp (ACC) release; *t*_2_: 10 minutes after ACC release; *t*_3_: 15 minutes after weaning from cardiopulmonary bypass; *t*_4_: the end of surgery.

^b^✓: refers to crucial events at corresponding points in time.

^c^Group A: amiodarone group.

^d^Group P: placebo-controlled group.

^e^Primary end point: occurrence of ventricular fibrillation (VF).

^f^Secondary end point: *t*_2_: the number and maximum energy of defibrillations to terminate VF; *t*_3_: heart rate, mean arterial pressure, mean pulmonary arterial pressure, central venous pressure; *t*_4_: the total dosages of vasoactive agents.

#### Anesthesia Protocols

All the patients will fast for 8 hours and abstain from water for 4 hours preoperatively and receive standardized general anesthesia. In the operating room, the patients will be routinely monitored including 5-lead electrocardiograph, peripheral blood oxygen saturation, invasive arterial blood pressure, bispectral index (BIS), and end tidal CO_2_, which will be recorded every 3 minutes in each patient’s electronic medical record. The induction of anesthesia will be performed as follows: 0.05 mg/kg midazolam, 0.3 mg/kg etomidate, 0.15 mg/kg cis-atracurium, and 4-6 μg/kg fentanyl. Approximately 5 minutes after induction, patients will be intubated and ventilated to maintain the end tidal CO_2_ at 35-45 mm Hg. Then, the ultrasound-guided central vein catheterization will be conducted via the right internal jugular or subclavian vein. Swan-Gans catheter will be floated to pulmonary artery through the right internal jugular. Thereafter, transesophageal echocardiogram will be inserted for the intraoperative cardiac estimations. The patients continued receiving anesthesia by inhalation of sevoflurane 1%-2% and continuous pump of propofol 1-2 mg/kg/hour, dexmedetomidine 0.5 μg/kg/minute, and cis-atracurium 0.05-0.1 mg/kg/hour. The total dosage of fentanyl will be 30-50 μg/kg. During continuation of anesthesia, the BIS will be maintained between 40 and 60. Inotropic agents, vasopressors, vasodilators, or fluid administration will be applied to achieve the following hemodynamic status: a mean blood pressure of 50-80 mm Hg, cardiac index (CI) ≥2.2 L/min/m^2^, and urine output ≥1.0 mL/kg/hour.

#### Surgical and CPB Procedures

The surgical procedures will be performed via median sternotomy with heparinization and standard CPB. The cannulation sites for CPB are at the discretion of the cardiac surgeon and dependent on the operation. The aortic cannulation is obtained with a patient size–appropriate cannula. Venous cannulation is obtained with a single 2-stage cannula in the right atrium or separate cannula in the superior and inferior vena cava. Anticoagulation is started with 400 μg/kg of heparin and maintained according to an activated clotting time of >480 seconds. CPB is initiated using a membrane oxygenator and the circuit is primed with 1500 mL of acetate Ringer solution and 200 mL of 50% human serum albumin. Patients are perfused by a nonpulsatile roller pump at a flow rate of 2.0-2.4 L/minute/m^2^ and with mean arterial pressure (MAP) of 50-80 mm Hg. Moderate systemic hypothermia around 30-32 °C is maintained during CPB. Myocardial protection is achieved using intermittent antegrade or retrograde infusions of histidine-tryptophane-ketogluterate cardioplegia. Cardioplegic infusion is repeated every 120 minutes or when electrical activity of the heart is detected. After weaning from CPB, reversal of heparin is achieved with protamine.

#### Management of VF

Thirty seconds before ACC release, 1 mg/kg of esmolol will be given to all patients. When VF occurs after ACC release, internal electrical defibrillation with 20 J will be performed in the first attempt. If not successful, the second defibrillation with 20 J will be attempted after reusing 0.5-1 mg/kg of esmolol. If VF persists, the third defibrillation with 30 J will be performed after giving 1 mg/kg of lidocaine. If VF termination is not achieved, the fourth defibrillation with 40 J will be attempted after administration of 50 mg of amiodarone. If VF still exists, administration of 100 mg of amiodarone and defibrillation with 50 J will be repeated until VF terminates.

### End Points

The primary end point is the incidence rate of VF 10 minutes after ACC release. The secondary end points include the duration of VF, the number and maximum energy of defibrillations needed to terminate VF, the use of other antiarrhythmic agents, and epicardial temporary pacemakers after ACC release. Besides, the secondary end points also include heart rate, MAP, mean pulmonary arterial pressure, central venous pressure and CI 15 minutes after anesthetic induction and weaning from CPB, and the speed of vasoactive agents at the end of CPB and surgery and their total dosages.

### Sample Size Estimation

The sample size is calculated based on the primary end point: the incidence rate of VF 10 minutes after ACC release using PASS (version 15.0; NCSS). According to the published studies, the incidence rate of VF after ACC release ranges from 45% to 100% [1-6]. We assumed that the incidence rate of VF 10 minutes after ACC release would be 70% in the placebo-controlled group and amiodarone could decrease the rate to 30%. To reach statistical significance with a power of 80% and an α value of .05 (2-sided), 21 patients are assessed to be needed in each group. Assuming a 20% dropout or missing data rate, we will recruit 27 patients in each group for a total of 54 patients.

### Statistical Analysis

All data will be analyzed using SPSS (version 22.0; IBM Corp) and in accordance with the intention-to-treat principle, beginning immediately after randomization. All statistical tests will be considered significant if *P*<.05. Only 2-sided tests will be used. Baseline characteristics will be described and compared by using the Fisher exact test for the categorical variables and 2-sample *t* test or Wilcoxon rank sum test depending on the normality of the data distribution for the continuous variables. The continuous variables will be described by mean and SD values if normally distributed or median and interquartile range if not. The normality of distributions will be checked graphically and using the Kolmogorov-Smirnov test. If there is a violation of distribution assumption, appropriate transformation will be used. The categorical variables will be expressed as frequencies and percentages.

For the primary end point, the incidence rate of VF 10 minutes after ACC release will be compared by using the chi-square test. For the secondary end points, heart rate, MAP, mean pulmonary arterial pressure, central venous pressure, and CI will be compared between 2 groups by using a repeated measures ANOVA model during the 2 observation times. Other continuous secondary end point variables will be compared between 2 groups by using a 2-sample *t* test or a Wilcoxon rank sum test depending on the normality of the data distribution. The chi-square test or Fisher exact test will be used to compare categorical secondary end point variables.

If data are missing at random, the analyses will be carried out using multiple imputations. The multiple imputation procedure will be based on all available data for that patient and be conducted using the chained equation approach. If data are not missing at random, the analyses will be conducted using available data with appropriate interpretational reservations. We will also evaluate the data using the intention-to-treat principle and per-protocol data set and compare the analysis results to estimate reliability of our analytical results.

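### The unadjusted primary test is valid but ignores LVH severity; prespecifying one echocardiographic covariate is a cheap improvement whose gain depends on an unproven association

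*Protocol article*

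**What the plan says.** The Statistical Analysis section of the protocol article fixes the primary comparison: "For the primary end point, the incidence rate of VF 10 minutes after ACC release will be compared by using the chi-square test". The Abstract names a different test for the same end point, "assessed using the Fisher exact test". Neither test uses any baseline value, and no covariate is named.

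Baseline data are summarised and also tested between arms: "Baseline characteristics will be described and compared by using the Fisher exact test for the categorical variables", with t or Wilcoxon tests for continuous variables. All tests are judged at two-sided P<.05.

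Every patient must have "left ventricular hypertrophy diagnosed by transthoracic echocardiogram" before surgery (Inclusion criteria). The Background gives the reason for choosing this population: "Left ventricular hypertrophy (LVH) has been found to increase the incidence rate of VF after ACC release". It adds a mechanism, namely poorer subendocardial supply and incomplete myocardial protection in hypertrophied hearts. Randomisation is in blocks of 4, with no stratification factor named.

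**The concern.** The trial is built on the premise that hypertrophy promotes reperfusion VF. If VF risk also rises with the degree of hypertrophy, that degree is a prognostic value fixed before randomisation. Neither the design as described nor the primary analysis uses it. In a trial of 54 patients a chance imbalance in such a value can be sizeable. Adjusting for it in a prespecified way removes that imbalance from the comparison and usually adds power without adding patients.

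What is at stake is some power in a small trial. The chance of detecting the design effect if it exists could be several points higher, for little effort.

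**Working it through.** **Inputs from the Sample Size Estimation section.** The VF rate "would be 70% in the placebo-controlled group and amiodarone could decrease the rate to 30"%. Power is 80%, two-sided alpha .05, with 21 per arm, raised to 27 for 20% dropout or missing data.

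**The plan's own figure.** With the unpooled normal approximation:

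n = [p1(1−p1) + p2(1−p2)] × (1.960 + 0.842)² / (p1−p2)² = (0.21 + 0.21) × 7.85 / 0.16 = 20.6, so 21 per arm.

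Dropout: 21 / 0.8 = 26.25, so 27 per arm. Both figures reproduce, so the sizing rests on an unadjusted comparison.

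**Exact power of the unadjusted Pearson chi-square test** (binomial enumeration, 70% v 30%): 74.8% at 21 per arm and 84.0% at 27. Its exact type I error when both rates are 50% is 4.6% and 4.2%, so it is slightly conservative.

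**Adjusted analysis, by simulation.** One standard-normal baseline covariate is used, with intercepts set so that the marginal rates stay at 70% and 30%. There were 6,000 trials per scenario, giving a Monte Carlo standard error of about 0.5 points: √(0.84 × 0.16 / 6,000) = 0.0047. The adjusted test is the logistic score test for arm. The odds ratio (OR) per SD of the covariate is an assumption.

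| Assumed OR per SD | Per arm | Unadjusted Pearson | Adjusted score test | Gain (points) |
|---|---|---|---|---|
| 1 (not prognostic) | 21 | 74.7% | 75.0% | 0.3 |
| 1 (not prognostic) | 27 | 84.4% | 85.7% | 1.3 |
| 1.5 | 27 | 84.6% | 87.7% | 3.1 |
| 2 | 21 | 75.2% | 79.3% | 4.1 |
| 2 | 27 | 84.5% | 89.1% | 4.6 |
| 3 | 21 | 74.3% | 83.6% | 9.3 |
| 3 | 27 | 83.4% | 91.5% | 8.1 |

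Further simulation runs agree to within about a point: roughly 5 points at OR 2 and 8 to 9 at OR 3. The gain at OR 1 cannot come from the covariate. It arises because Pearson runs below 5% while the score test runs at or just above it, so about 1 to 2 points of every gain should be read that way.

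**Type I error of the score test** (both rates 50%): 4.9% to 5.4% at 27 per arm and 5.0% to 6.0% at 21.

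**Can the data carry the model?** At the planning rates, expected VF events at 27 per arm are 27 × 0.7 + 27 × 0.3 = 27, with 27 non-events. That is enough for arm plus one covariate, but not for a long list.

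**Side check on the baseline tests.** At 27 per arm the largest standardised difference that is still non-significant is t(.975, 52) / √13.5 = 2.007 / 3.674 = 0.55 SD. A difference of 0.5 SD gives t = 0.5 × 3.674 = 1.84, P=.07. Under sound randomisation any difference is chance, so such a P value informs about neither cause nor importance.

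**The case against.** The case against is substantial, and most of it stands.

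- **The unadjusted test is not wrong.** A reader might infer that leaving out severity biases or invalidates the primary result. It does not: the test's error rate already allows for chance imbalance, and the test agrees with the sizing. Adjustment is an option for improvement.
- **The power is neither shown nor free.** A reader might infer that the Background establishes severity as prognostic here. It compares hypertrophied hearts with others, whereas every patient in this trial has hypertrophy. Nothing is said about gradation within that group, and no wall thickness, mass or grade is named as collected. The gain may be close to nil, and part of it comes from a less conservative test.
- **The absent effect estimate is not a finding.** A reader might infer that only a P value will be reported. The section says categorical variables will be given as counts and percentages, and an article may leave an effect measure and its interval to the full protocol or analysis plan.
- **Baseline data are not used for significance tests alone.** They are also described, and they can enter the multiple imputation. Nothing says that baseline P values will decide balance or trigger adjustment.
- **The change is not trivial in timing.** The Results section reports 21 patients already recruited, so this would amend a primary analysis mid-trial.

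What survives is that the article fixes an unadjusted method in writing, a likely source of a prognostic value exists for every patient, and adjusting for it costs almost no power even if it proves uninformative.

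**Conclusion.** The point holds as a recommended improvement to a valid analysis. Adding one prespecified echocardiographic severity covariate would be expected to gain at most about 1 to 2 points of power if it is not prognostic (owing to Pearson's conservatism), about 5 points at an OR of 2 per SD, and about 8 to 9 points at an OR of 3. At 21 evaluable patients per arm, where exact Pearson power is 74.8%, an OR of 2 to 3 would bring power to about 79% to 84%.

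These sizes rest on the plan's 70% v 30%, on a roughly normal covariate with a linear effect on the log odds, and on an assumed association that the documents do not supply. The price is a type I error of about 5% to 6%, against 4.2% to 4.6% for Pearson.

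The baseline significance tests are a minor side issue. They are uninformative under randomisation, and removing them changes no primary result.

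**What to change.** Before any unblinded look at outcomes:

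1. Name one covariate from the preoperative echocardiogram, for example LV wall thickness. State how it is measured, that it enters as a continuous linear term, and how a missing value is handled.
2. Make the primary analysis a logistic model of VF on arm plus that covariate, and test arm with the score test.
3. Report the standardised risk difference with a 95% CI. A conditional odds ratio would not be comparable with the 40-point difference (70% − 30%) used for sizing.
4. Keep the unadjusted comparison as a sensitivity analysis. State which test it is, since the Abstract and the Statistical Analysis section name different ones.
5. Describe baseline characteristics by arm without significance tests.

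The cost is a paragraph of analysis text, one value abstracted per patient (including, blind to outcome and arm, the 21 already recruited), and a dated amendment. It assumes that the echocardiogram reports record the chosen measure; this should be checked before the covariate is fixed.

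### The Abstract and the Statistical Analysis section name different tests for the primary end point, and the form of the chi-square test is left open

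*Protocol article*

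**What the plan says.** The Abstract (Methods paragraph) states that the primary end point will "be assessed using the Fisher exact test". The Statistical Analysis section states that "the incidence rate of VF 10 minutes after ACC release will be compared by using the chi-square test". It does not say whether a continuity correction is applied. That section leaves a choice between chi-square and Fisher only for categorical secondary end points, and assigns Fisher to categorical baseline variables.

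The decision rule is common to both tests: P below .05 and "Only 2-sided tests will be used".

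The Sample Size Estimation section assumes that the rate of VF "would be 70% in the placebo-controlled group and amiodarone could decrease the rate to 30" per cent. It reports that "with a power of 80% and an α value of .05 (2-sided), 21 patients are assessed to be needed in each group", and continues: "Assuming a 20% dropout or missing data rate, we will recruit 27 patients in each group for a total of 54 patients". It does not name the test behind the calculation.

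**The concern.** The trial has one primary end point and one success criterion, and the article attaches two tests to it. With 27 patients per arm the two need not agree. The uncorrected Pearson chi-square can slightly exceed the nominal 5% level, whereas Fisher's exact test runs at about half of it. Some observed tables would therefore count as a positive trial under one sentence and a negative trial under the other. The stated 80% power also cannot be attached to the primary analysis until it is known which test that is.

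**Working it through.** **Inputs.** 70% vs 30%, two-sided α of .05, 80% power, 21 per arm before and 27 per arm after the 20% allowance (Sample Size Estimation); 1:1 allocation (Randomization and Blinding); significance at P<.05 (Statistical Analysis).

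**The plan's own figure.** The unpooled normal approximation reproduces it:

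n = (1.960 + 0.842)² × (0.7×0.3 + 0.3×0.7) / 0.4² = 7.849 × 0.42 / 0.16 = 20.6, rounded up to 21.

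Allowing for 20% loss: 21 / 0.8 = 26.25, rounded up to 27. So 21 and 27 follow from an approximation, not from the exact behaviour of either named test.

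**Single tables at 27 per arm.** For a vs b events, the uncorrected Pearson statistic is

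X² = 54 × [a(27−b) − b(27−a)]² / [(a+b)(54−a−b) × 27²].

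For 18 vs 10: 54 × (18×17 − 10×9)² / (28 × 26 × 729) = 54 × 216² / 530,712 = 4.747, P=.029.

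For 19 vs 11: 54 × (19×16 − 11×8)² / (30 × 24 × 729) = 54 × 216² / 524,880 = 4.800, P=.028.

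| Events, placebo vs amiodarone (of 27) | Pearson, uncorrected | Yates-corrected | Fisher exact |
|---|---|---|---|
| 17 vs 9 (63% vs 33%) | .029 | .057 | .056 |
| 18 vs 10 (67% vs 37%) | .029 | .057 | .056 |
| 19 vs 11 (70% vs 41%) | .028 | .055 | .054 |
| 20 vs 12 (74% vs 44%) | .027 | .053 | .051 |

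**All tables.** Each of the 28 × 28 possible tables was classified by each test at P<.05. Fifty-two tables (26 in each direction) are significant by uncorrected Pearson and not by Fisher; none go the other way. Yates and Fisher disagree on none.

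**Power and type I error.** Exact power is the sum of Bin(a; n, 0.7) × Bin(b; n, 0.3) over the tables that a test rejects. Maximum type I error uses the same sum with equal rates, maximised over common rates from 0.01 to 0.99.

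| | Pearson, uncorrected | Yates-corrected | Fisher exact |
|---|---|---|---|
| Power, 27 evaluable per arm | 84.0% | 76.3% | 76.3% |
| Power, 21 evaluable per arm | 74.8% | 62.9% | 62.9% |
| Maximum type I error, 27 per arm | 5.7% | 2.6% | 2.6% |

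Fisher rejects no table that Pearson does not, so the power gap is also the probability under the design rates that the two disagree: 84.0 − 76.3 = 7.7 points at 27 per arm and 74.8 − 62.9 = 11.9 points at 21. Fisher first reaches 80% power at 29 evaluable per arm (81.4%).

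**A smaller effect.** At 70% vs 40% with 27 per arm, power is 58.6% by Pearson and 48.1% by Fisher, a gap of 10.5 points.

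**The case against.** The strongest reply is that the Statistical Analysis section is the operative text and names one test for the primary end point, so the Abstract is merely out of step. There is support for this: the Abstract also gives a 30-minute window for the end point where the Methods sections give 10 minutes. Most analysts would follow the Methods, and a fuller protocol or analysis plan may already settle the matter. This bears on how the conflict probably arose. It does not remove it: both sentences are current text, the article gives neither precedence, and the operative section still does not say which chi-square is meant.

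The second reply is that the numerical consequences depend on that form. This stands. With the Yates correction at 27 per arm, the chi-square and Fisher give the same verdict on every table. A reader might infer that the two named tests necessarily lead to opposite verdicts and differ by about 8 points of power; the article does not support that without the assumption of an uncorrected test.

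A reader might also infer that the wording was left open so that the test could be picked after the results are seen. The wording would permit that, but nothing in the article shows that it is intended.

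**Conclusion.** The contradiction is real and concerns the trial's single success criterion. Its size is conditional. If the chi-square is uncorrected Pearson and all 27 per arm are evaluable, 7.7% of trials under the design rates would be positive by chi-square and negative by Fisher. Fisher would then fall below the planned 80% power, while Pearson would exceed both that power and, for some common event rates, the 5% level. If the chi-square carries the Yates correction, the conflict at 27 per arm is one of wording only, but the stated 80% power is then not met by either test.

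The figure of 27 evaluable per arm does not flatter the case: at the 21 that the plan expects after losses, the gap between uncorrected Pearson and Fisher is wider and neither reaches 80% power under the design rates.

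**What to change.** Before unblinding, name one primary test and its exact form, including whether a continuity correction is used, in identical terms in the Abstract and the Statistical Analysis section. State in the Sample Size Estimation section the power that this test delivers.

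- If uncorrected Pearson is kept: report 84.0% power at 27 evaluable per arm, and acknowledge that its maximum type I error is 5.7%, slightly above the nominal level.
- If Fisher is kept: restate the power as about 76% at 27 evaluable per arm. The same figure applies to a Yates-corrected chi-square.
- Optional: an unconditional exact test (Boschloo) has 83.7% power and a maximum type I error of about 4.5% at 27 per arm. It holds the 5% level with little loss of power, but it may have to be run outside SPSS, the package that the article names for all analyses. This is a preference and is not needed to cure the contradiction.
- Optional: report the risk difference with a 95% interval beside the P value.

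The cost is a wording change in two or three places. With 21 of 54 participants recruited when the article was written, nothing in the conduct of the trial has to change.
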